# Efficacy of a culturally tailored cognitive-behavioural intervention for Ethiopian children with haematological malignancies: study protocol for randomised controlled trial

**DOI:** 10.1186/s13063-022-06768-x

**Published:** 2022-09-27

**Keywords:** Cognitive-behavioural intervention, Children, Haematological malignancy

## Abstract

**Background:**

Paediatric cancer patients often experience anxiety and depression. Evidence suggests that cognitive-behavioural interventions may help reduce anxiety and depression in children undergoing cancer treatment. However, only a few studies evaluated its impact on the psychological well-being and quality of life of paediatric cancer patients globally. In Ethiopia, there has been no published study to date. Thus, this trial aims to evaluate the efficacy of a culturally tailored cognitive-behavioural intervention for Ethiopian children with haematological malignancies receiving chemotherapy.

**Methods:**

A single-blinded, parallel-group, two-arm, repeated measure randomised controlled trial will be conducted. Eighty children aged 8 − 18 years with haematological malignancy receiving chemotherapy will be recruited and randomly assigned to experimental or control groups. The experimental group will receive five sessions of introducing cognitive-behavioural intervention, identifying and modifying maladaptive thoughts and behaviour, behavioural activation, practising deep breathing exercises, reassessing goals or treatment plans, and encouraging participants to maintain changes. Each session will be conducted face-to-face for 30–35 min a week. The control group will receive usual care. The outcomes will be measured at baseline, post-intervention, and one month after the intervention using the Revised Child Anxiety and Depression Scale and Paediatric Quality of Life Inventory Generic Core Score 4.0.

**Discussion:**

The findings of this study will provide evidence to support the integration of culturally effective cognitive-behavioural intervention strategies into paediatric oncology practice and thus, add new knowledge to the literature and help improve the care of children with haematological malignancies receiving chemotherapy. If the cognitive-behavioural intervention is shown to be effective and culturally acceptable, it will provide evidence to include the intervention as a standard of care in paediatric haematology/oncology.

**Trial registration:**

ClinicalTrials.gov NCT05270655. Registered on March 8, 2022.

**Supplementary Information:**

The online version contains supplementary material available at 10.1186/s13063-022-06768-x.

## Background

Haematological malignancies include malignancies of the blood, bone marrow, and lymph nodes. Leukaemia, lymphoma, and myeloma are the most common types of paediatric cancer all over the world [1–3]. In Ethiopia, evidence shows that more than 50% of childhood cancers are haematological malignancies [4, 5].

The course of childhood cancer causes various stressful symptoms among children [6]. The diagnosis, course of treatment such as painful medical procedures and chemotherapy side effects, and challenges in social life such as missing the opportunity to play with friends, separation from family members, and school absence are major stressors among children [7, 8]. Although most paediatric cancer patients experience various psychological problems, anxiety and depression are among the most frequently reported problems [9, 10]. Childhood cancer also significantly impedes their quality of life (QOL) [11–16].

Poorly managed anxiety and depression significantly impact QOL and survival status [17, 18]. Unmanaged anxiety predicts fatigue [7], anticipatory pain, nausea and vomiting during the subsequent medical procedures [19] and increases off-therapy anxiety [20]. Poorly treated depression impairs relationships and psychological functioning [21], increases the burden of symptoms and mortality [9], and affects motivation to change behaviour and evidence suggests these patients are less likely to adhere to treatment [22]. Non-adherence to treatment including chemotherapy decreases prognosis increases relapse [23, 24], morbidity and hospital readmissions [17] and treatment costs, and has a negative impact on QOL [25]. Likewise, poor QOL is associated with emotional, behavioural, and social problems such as difficulty establishing or maintaining friendships and poor school performance [26].

Psychosocial problems, such as anxiety and depression in children with cancer are given little attention and are poorly managed [27] as more emphasis is given to the physical aspect of the illness. Thus, a tailored psychosocial intervention that has been found to be effective should be incorporated into the current medical treatment [9]. Psychosocial interventions including music-based interventions [28–30], art therapies [31–34], play-based interventions [35–37] and cognitive-behavioural interventions (CBI) [38–40] show promising effects in improving the health outcomes of children with cancer. Among psychosocial interventions, CBI is most frequently recommended to manage anxiety and depression in paediatric cancer patients due to its effectiveness and feasibility [38–41].

Evidence suggests that CBI helps improve psychosocial and health-related outcomes in children with cancer [42–46]. However, as most previous studies were conducted in developed countries, adopting and applying CBI approaches and strategies in other countries might be ineffective. In addition, in most studies, the theory guiding CBI development was not identified. Thus, developing and evaluating a theory-guided CBI in a different country such as Ethiopia is essential.

CBI is a structured and tailored psychotherapeutic intervention based on cognitive and behavioural approaches [47, 48], and helps to modify distorted thinking and beliefs, reduce maladaptive behaviour, and increase coping skills [49]. CBI enables patients to manage their problems independently and to maintain behavioural changes [47, 50].

In this study, we developed a CBI for children with haematological malignancies guided by Beck’s cognitive model [50]. The model describes the associations among cognition, emotion, and behaviour [47]. Distorted thoughts and unhelpful coping strategies often cause emotional problems such as anxiety and depression [51–53]. For instance, in Ethiopia, most patients experience extreme stress as they believe that there is no hope of childhood cancer being cured with modern medicine. They abandon treatment because they believe religious and spiritual therapies, or alternative forms of treatment such as visiting traditional healers and using holy water, are more effective [54, 55]. Thus, CBI strategies help identify and modify distorted thoughts and unhelpful behaviour [48] and promote the development of positive coping strategies, and cognitive and behavioural adaptation [47, 56]. Positive changes in the cognitive process and development of positive coping behaviour help reduce stressful feelings such as anxiety and depression and, in turn, could improve psychosocial functioning and QOL [57].

## Methods

### Objectives

The objectives of this study are to evaluate whether a theory-based CBI achieves (1) reduced anxiety and depression and (2) improved quality of life post-intervention in the experimental group compared to the control group receiving usual care.

### Study design

This trial is designed as a multi-centre, assessor-blinded, two-arm parallel-group, repeated measure randomised controlled trial (RCT). The protocol for this trial was registered at ClinicalTrials.gov (NCT05270655). A multi-centre trial helps recruit adequate and representative participants and thus, improves the generalisability of the study findings [58].

The schedule of enrolment, interventions and assessments of the study protocol follows the Standard Protocol Items: Recommendations for Interventional Trials (SPIRIT) Figure (Fig. 1) and SPIRIT Checklist (Additional File 1) [59].

**Fig. 1 Fig1:**
[figure not shown]
SPIRIT figure

### Study setting

Participants will be recruited from the paediatric haematology-oncology wards in two university-affiliated specialised hospitals. These hospitals are among the largest specialised hospitals providing medical services to many children with cancer in Ethiopia.

### Participants

Participants (1) aged 8 to 18 years old, (2) diagnosed with haematological malignancy, (3) undergoing chemotherapy, (4) able to communicate in Amharic, and (5) with written parental consent and oral child assent will be recruited. Participants (1) with evidence of developmental, psychological and/or psychiatric illness or problems**,** (2) unable to collaborate in the study due to acute illness, and/or (3) having hearing or speech problems that could affect the study process will be excluded.

### Sample size

The sample size was estimated using the G*Power (version 3.1.9.7) sample size calculator based on the effect size of CBI on anxiety, the primary outcome of this study. Evidence shows that the effect size of CBI ranges from 0.7 to 3.9 [43, 45, 46, 60]. Using the smallest effect size of 0.7, 80% power, 5% significance level and a potential 15% attrition rate, 80 participants (40 per group) will be recruited.

### Participant recruitment

A research assistant (RA) in each hospital with the help of nurses in the paediatric oncology ward will approach children and their parents to identify their eligibility, explain the study procedures, and provide a detailed information sheet. For participants who agree to join the study, the RA will obtain written parent consent and oral child assent, collect baseline clinical and demographic data, and provide the participants with an appointment card.

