### Randomisation

Participants will be stratified based on their age groups, i.e. ≤ 12 years and ≥ 13 years in each hospital [61]. Evidence shows that age influences the level of anxiety, depression, and QOL [11, 62, 63]. Stratified randomisation balances comparability between the groups and increases the power of the study [64]. The principal investigator will generate a computerised random sequence with a 1:1 allocation using a block size of 4 and 6 for each stratum of each hospital.

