### Experimental group

The experimental group will receive five weekly face-to-face sessions (30–35 min each). The intervention will be delivered by two psychologists with master’s degree who have clinical and research experience in CBI. The contents include (1) an introduction to CBI, (2) identifying, evaluating, and challenging maladaptive thoughts, beliefs and behaviour, (3) behavioural activation, (4) practising deep breathing exercises, and (5) reassessing goals or treatment plans, and encouraging participants to maintain changes.

The intervention will be delivered in the hospital before the children undergo chemotherapy to avoid excessive fatigue and increase their engagement with the interventions. Additionally, to establish a strong family support system and enhance intervention delivery, parents or primary caregivers of the child will be invited to attend the introduction of the first session, the summary of each session, and whenever else necessary. However, the role of the parents/caregivers is only to facilitate the intervention delivery, such as providing information when needed.

To enhance the retention rate, interventions will be delivered during participants’ medical appointments at the hospitals. In addition, each participant will be provided with an appointment card containing the date and time of the next CBI appointment, and the RA will remind them with a phone call 2 days before the next appointment. The participants will continue receiving the usual psychosocial care provided by the nurses in the paediatric oncology ward.

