### Control group

The control group will receive the usual psychosocial care such as information and health education about the course of the illness and treatments provided by the nurses in the paediatric oncology ward. Additionally, the RA will offer them attention every week for 30 min about treatment adherence and other concerns. Parents will be invited to attend if they wish to do so.

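### The research assistant who screens and consents also learns past allocations through arm-specific contact, so under blocks of 4 and 6 the next allocation can be guessed better than chance and selection bias could enter

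*Protocol article*

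**What the plan says.** - **Who controls entry.** Participant recruitment: one RA per hospital "with the help of nurses in the paediatric oncology ward will approach children and their parents to identify their eligibility". For families who agree, "the RA will obtain written parent consent and oral child assent, collect baseline clinical and demographic data".
- **What needs judgement.** Participants: exclusion (2) covers children "unable to collaborate in the study due to acute illness", with no threshold. Exclusion (1), which extends to psychological problems, also leaves some room.
- **How the sequence is built.** Randomisation: the principal investigator generates "a computerised random sequence with a 1:1 allocation using a block size of 4 and 6 for each stratum of each hospital". The strata are two age groups in each of two hospitals, so four in all.
- **How it is hidden.** Allocation concealment: RAs, among others, are said not to know the group, and the sequence is kept in numbered opaque envelopes that stay sealed until assignment.
- **What the RA does afterwards.** Experimental group: "the RA will remind them with a phone call 2 days before the next appointment". Control group: "the RA will offer them attention every week for 30 min about treatment adherence and other concerns".
- **Who is blinded.** Blinding: only the outcome assessors, who are nurses from outside the study hospitals.

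**The concern.** Both post-randomisation tasks depend on the arm: a child with a CBI appointment gets the reminder call, and a control gets the weekly talk. The RA therefore learns the arm of each enrolled child. The article describes one RA per hospital and no separation of duties, so the natural reading is that the person who screens the next child has seen the allocations so far in both age strata of that site.

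Permuted blocks return to balance every 4 or 6 children. Someone who has seen the earlier allocations can bet on the arm that is behind. An envelope does not prevent this, because the information comes from cards already opened. Acute illness during chemotherapy varies from day to day, so enrolling a child today or waiting is easily defended either way. A hunch about the next arm could tip that decision without any intent.

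At stake is the comparability of the arms in prognosis. Blinded assessment does not help, because the selection would happen before any outcome is measured. The primary outcome is self-reported anxiety, which acute illness may plausibly affect.

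**Working it through.** **Inputs.** From the article: 1:1 allocation, blocks of 4 and 6, four strata, 80 children, planning effect 0.7 SD. Assumed: 20 children per stratum (80/4), blocks of 4 and 6 equally likely and in random order, and an RA who sees all earlier allocations in the stratum.

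**The plan's own figure.** A two-sample t-test with effect 0.7, two-sided 5% and 80% power needs 34 per arm. 34/(1 - 0.15) = 40 per arm, so the total of 80 reproduces. The sample size is not in dispute; 0.7 is used below only as a yardstick.

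**Step 1: guessing within one complete block.** For a block of size b = 2m, guessing the arm that is behind gives an expected number correct of m + (2^b / C(b,m) - 1)/2.
- b = 4: 2 + (16/6 - 1)/2 = 2.833, and 2.833/4 = 70.8%.
- b = 6: 3 + (64/20 - 1)/2 = 4.1, and 4.1/6 = 68.3%.
- Equal mix of complete blocks: (2.833 + 4.1)/(4 + 6) = 69.3%.

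**Step 2: the mixed sequence, cut at 20 per stratum (simulation).** The RA guesses the arm that is behind and needs no knowledge of block sizes.
- A guess is possible for 60.7% of enrolments; the arms are tied for 39.3%.
- 48.9% of enrolments are guessed correctly and 11.9% wrongly.
- Correct when a guess is made: 48.9/60.7, about 80%.
- Correct overall, ties counted as half: 48.9 + 39.3/2, about 68.5%.

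**Step 3: how much is certain.** In a block of known size, the share of allocations known for sure is [2m/(m + 1)]/b: 33% for size 4 and 25% for size 6. With the two sizes mixed and their order unknown, simulation gives about 6%. About 29% can then be called with at least 80% confidence. Mixing the sizes removes most of the certainty but hardly changes the average success rate.

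**Step 4: from guessing to bias.** Suppose discretion shifts the mean prognosis of a child by x SD when an arm is guessed. By symmetry, a child who ends up in CBI was guessed CBI with probability 0.489 and guessed control with probability 0.119; the reverse holds for controls.
- Selection only when one arm is expected: 0.489x - 0.119x = 0.37x.
- Opposite shifts for the two arms: each arm moves by (0.489 - 0.119)x = 0.37x in opposite directions, so the difference is 0.74x.

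| Assumed x | 0.37x | 0.74x |
|---|---|---|
| 0.1 SD | 0.037 | 0.074 |
| 0.3 SD | 0.111 | 0.222 |

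Against 0.7, this runs from 0.037/0.7 = 5% to 0.222/0.7 = 32%. Both columns assume that the RA acts on every enrolment with a guess, and neither allows for the T0 measurement.

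**The case against.** The strongest case against has five parts.

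**Concealment is provided for.** A reader might infer that concealment fails outright, or that the Allocation concealment section contradicts the RA's later duties. The text does not support that. The envelopes are of a sound kind, block sizes are mixed, and few allocations are certain if the 4/6 order is random and unknown. The statement that RAs would not know the group can be true until assignment; it cannot be true afterwards. What stands is that the section does not draw this line, and that envelopes do not stop better-than-chance guessing.

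**Selection is not shown.** The RA does not deliver the CBI (psychologists do), nurses help with screening, and no motive appears. The article does not say that the RA alone rules on acute illness. This stands: the point is an opportunity, not an event.

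**The size is assumed.** Nothing in the article supports a shift of 0.1-0.3 SD, and the upper multiplier needs selection in both directions. Deferral only when one arm is expected gives half. This stands, and the range is reported accordingly.

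**The analysis may help.** A reader might infer that the planned GEE can do nothing about such selection. That is too strong. Anxiety is measured at T0 and the model has a group-by-time term, so selection on baseline anxiety would show at T0 and be partly netted out. Selection on prognosis that T0 anxiety does not capture would remain.

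**It is late.** Recruitment began in May 2022, the study is to end in November 2022, and T2 is at 10 weeks. Counting back 70 days from 30 November gives 21 September for the last enrolment, before publication on 27 September. Few or no enrolments may remain, so the retrospective part of the fix carries most of the weight.

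**Conclusion.** The point holds as a risk created by the division of tasks. The person who identifies eligibility and takes consent at each hospital also sees past allocations, and can guess the next one correctly about 68-69% of the time instead of 50%. This rests on about 20 children per stratum, random block order, and the reading that the same RA does all the tasks at a site, which the article implies and nowhere qualifies. Knowledge of the block sizes is not needed.

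The possible bias is 0.37x to 0.74x, or 0.04-0.22 SD for an assumed x of 0.1-0.3, before any reduction from the T0 comparison. A reader might take the upper end, about a third of the planning effect, as the expected bias. The documents do not support that: it needs the largest assumed shift, opposite selection for both arms, action on every guess, and no correction from baseline.

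**What to change.** 1. **Separate judgement from knowledge of allocations.** Have the site supervisor at each hospital (the paediatric haematologist-oncologist named under Oversight and monitoring, with no stated arm-specific contact) confirm exclusions (1) and (2) and sign a consecutive screening log that records every child approached, including those deferred.
2. **Fix the order of steps.** Complete consent and T0 before the envelope is opened, and have it opened by someone other than the screening RA.
3. **Correct Allocation concealment** to say that RAs are unaware of the group only until assignment.
4. **For children already enrolled,** disclose the overlap of roles and compare baseline characteristics, including T0 anxiety, by the arm predicted from earlier allocations in the stratum. Report this as a description. About 0.607 x 80, or 49 children, would have a prediction, roughly 24 per predicted arm. The difference detectable with 80% power is then about (1.96 + 0.84) x sqrt(2/24) = 0.81 SD. A null result would therefore not exclude shifts of the size considered here.

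Cost: a signature and a few minutes per enrolment, with no new staff, plus one descriptive table.

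Replacing the blocks by a big-stick rule with a limit of 3 is not advised. In simulation it lowers correct guesses to about 57%, but makes about 14% of assignments certain to anyone who knows the limit, and little of the sequence is likely to remain.

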### Randomisation

Participants will be stratified based on their age groups, i.e. ≤ 12 years and ≥ 13 years in each hospital [61]. Evidence shows that age influences the level of anxiety, depression, and QOL [11, 62, 63]. Stratified randomisation balances comparability between the groups and increases the power of the study [64]. The principal investigator will generate a computerised random sequence with a 1:1 allocation using a block size of 4 and 6 for each stratum of each hospital.

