### Data analysis

The analysis will be conducted using Statistical Package for the Social Sciences (IBM SPSS statistics 26). To check discrepancies in data entry, the principal investigator and a RA will independently enter the coded data twice into SPSS. While categorical data will be summarised using frequencies and percentages, continuous data will be summarised using means, standard deviations, median and interquartile ranges depending on normality distribution. Depending on the types of data and normality distribution, the characteristics of the groups will be compared using independent t-tests, Mann–Whitney U tests, Chi-square tests, and Fisher’s exact tests. Outcome analysis will be conducted as an intention-to-treat analysis. Missing value analyses will be conducted to determine the need for multiple imputations. A generalised estimation equation (GEE) model will be applied to determine the intervention effect between the groups in terms of a group, time, and group*time interaction. Variability in effect will be assessed by performing a sub-group analysis. Given that this trial is studying a low-risk or no-risk intervention, there are no stopping rules or plans for interim analyses. The significance level will be determined at 5% (two-sided) for all statistical tests.

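### Stratification by age group and hospital is credited with extra power, but the stated GEE omits both factors: a follow-up comparison becomes mildly conservative, and a group-by-time comparison gains nothing

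*Protocol article*

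**What the plan says.** The Randomisation section sets the strata: "Participants will be stratified based on their age groups, i.e. ≤ 12 years and ≥ 13 years in each hospital". The Study setting section names two hospitals, so there are four strata. Allocation is "1:1 allocation using a block size of 4 and 6 for each stratum of each hospital".

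Two reasons are given for stratifying. One is prognostic: "Evidence shows that age influences the level of anxiety, depression, and QOL". The other is statistical: "Stratified randomisation balances comparability between the groups and increases the power of the study".

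The Data analysis section describes the GEE by three terms. The "model will be applied to determine the intervention effect between the groups in terms of a group, time, and group*time interaction". Neither age group nor hospital is among them, and the T0 score is not named as a covariate. A sub-group analysis is mentioned without detail. The section does not say which term or contrast tests the primary outcome, anxiety, measured at T0, T1 (6 weeks) and T2 (10 weeks).

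**The concern.** Stratified allocation removes differences between strata from the comparison of the groups. A model that leaves the strata out still counts those differences as residual noise, so its standard error can exceed the true sampling variation of the estimate. The test then rejects too rarely under the null, and part of the precision bought by the design is not used.

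Whether this happens depends on the contrast. A difference between groups at a follow-up visit is affected. A difference in change from baseline is not, provided the stratum effects are the same at every visit. Because the article does not name the contrast, both readings have to be checked. At stake is modest efficiency and a correctly sized confidence interval, not bias.

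**Working it through.** **Inputs from the article.** Effect size 0.7, 80% power, 15% attrition and 80 children (Sample size); 5% two-sided (Data analysis); four strata, 1:1, blocks of 4 and 6 (Randomisation); three visits (Outcomes and measurements).

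**Assumptions, none of them in the article.** The strata explain a share R² of 5%, 10% or 20% of the outcome variance, constant over time. The correlation between a child's scores at two visits is 0.5. Outcome variance is 1. There are 68 completers, 34 per group, balanced within strata.

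**Step 1: the plan's own figure.** A two-sample t-test with d = 0.7, 5% two-sided and 80% power needs 34 per group, 68 in total; 68 / 0.85 = 80. This reproduces the stated size. It takes no credit for stratification.

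**Step 2: group difference at one follow-up visit.**
- SE reported without strata: √(2/34) = 0.2425. True SE: 0.2425 × √(1 − R²). Ratio: 1/√(1 − R²).
- Actual type I error: 2Φ(−1.96/√(1 − R²)).
- Power without strata: Φ((0.7/0.2425 − 1.96)/√(1 − R²)) = Φ(0.926/√(1 − R²)).
- Power with strata: Φ(2.886/√(1 − R²) − 1.96).

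| R² | SE too large by | Type I error | Power without strata | Power with strata | Loss (points) |
|---|---|---|---|---|---|
| 5% | 2.6% | 4.4% | 82.9% | 84.2% | 1.3 |
| 10% | 5.4% | 3.9% | 83.6% | 86.0% | 2.4 |
| 20% | 11.8% | 2.8% | 85.0% | 89.7% | 4.7 |

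At R² = 0 the same formula gives 82.3%.

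Simulating this comparison gave power of 81.2%, 81.5% and 83.2% without strata and 82.6%, 84.3% and 88.3% with them: losses of 1.4, 2.8 and 5.1 points.

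A GEE simulation (exchangeable correlation, robust SE, three visits, 1,000 runs per setting) gave losses of 1.3, 2.5 and 5.0 points. At R² = 20% and d = 0.7 its reported SE was 0.238 against an empirical 0.217; with strata it was 0.211 against 0.216. In that simulation the adjusted test rejected 5.5% to 6.1% of the time under the null (simulation error √(0.05 × 0.95/1000) = 0.7 points), so robust SEs may run slightly small at this size.

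Taken together, the loss is about 1, 3 and 5 points.

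**Step 3: group-by-time term.** A stratum effect that is equal at T0 and T1 drops out of the change. The variance of the change is 2 × (1 − 0.5) = 1 for every R², so the SE is again 0.2425. Simulated power was 81.1%, 81.6% and 81.2% without strata and 81.0%, 81.7% and 81.1% with them. In the GEE simulation, SE and power were identical with and without strata (at R² = 20%: 0.238 and 81.7% in both). Stratification neither inflates this SE nor adds power to this test.

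**Step 4: T0 score as a covariate.** Residual variance with the T0 score alone is 1 − 0.5² = 0.75. With strata as well it is (1 − R²) − (0.5 − R²)²/(1 − R²), which gives 0.737, 0.722 and 0.688. Simulated power was 90.0%, 90.4% and 90.7% with the T0 score alone and 90.0%, 90.9% and 92.3% with strata added: gains of 0, 0.5 and 1.6 points from the strata. At R² = 20% and d = 0.7, the reported SE moves from 0.211 (empirical 0.206) to 0.202 (empirical 0.205).

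**The case against.** The strongest reply is that, with T0 kept as an outcome, the intervention effect is normally read from the interaction, and the stated model includes one. Step 3 shows that this contrast loses nothing by omitting the strata. That stands. A reader might infer that the omission inflates the standard error of every between-group comparison; it does not. The reply does not rescue the power rationale, though, because under that reading stratification adds no power.

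A second reply is that an article condenses the full plan, which may name the strata as covariates. Nothing in the article says they are excluded, so that cannot be ruled out. But the article does list the model's terms and does claim a power gain, and the two do not meet as written.

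Third, the power remark is a general rationale and not a quantified promise, any error is in the conservative direction, and the sample size does not depend on it. All of this stands and limits the weight of the point.

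A reader might also infer that the whole gain from stratification is lost. In the follow-up reading that is too strong. Balance lowers the true sampling variation, so power rises from 82.3% to 85.0% at R² = 20% even without adjustment: 2.7 of the 7.4 points available (89.7 − 82.3).

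**Conclusion.** The point holds in a limited form. The stated model does not use the strata to which the Randomisation section attributes extra power. For a group difference at T1 or T2, or averaged over time, the SE is too large by 2.6% to 11.8% and the loss is about 1 to 5 points of power, for strata explaining 5% to 20% of variance. For the group-by-time term there is no inflation and no gain, and adding stratum main effects changes nothing.

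The sizes rest on the assumed R², stratum effects constant over time, a correlation of 0.5 and balanced strata. The article supplies none of these figures; it says only that age matters. It would be wrong to infer that the trial is underpowered or its test invalid: the 80 children and the 80% power stand, and the error is conservative. It is worth correcting because the remedy is cheap and the contrast for the primary outcome needs naming in any case.

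**What to change.** State, before the data are analysed by group, that the T1 and T2 scores of each outcome are modelled by GEE with group, time, group-by-time, the T0 score, age group (≤ 12, ≥ 13) and hospital. State also which group difference (at T1, at T2, or averaged over both) tests anxiety.

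This moves T0 from outcome to covariate, so it changes the model rather than only adding terms; adding the strata to the present model would leave the interaction unchanged. Most of the benefit comes from the T0 score (about 81% to 90% power at a correlation of 0.5). The strata add 0 to 2 points and bring the reported SE into line with the design.

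The cost is one sentence of analysis wording and three degrees of freedom. Children with neither T1 nor T2 would then contribute only through the multiple imputation that the article leaves open.

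A separate, minor matter: under Data analysis "the characteristics of the groups will be compared using independent t-tests" and similar tests. If these are baseline comparisons, as they appear to be, a descriptive table would serve better, since such tests cannot show which covariates matter. The point above does not depend on this.
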